## Abstract

**Background:**

The incidence of oropharyngeal cancer is increasing in the developed world. This has led to a large rise in research activity and clinical trials in this area, yet there is no consensus on which outcomes should be measured. As a result, the outcomes measured often differ between trials of comparable interventions, making the combination or comparison of results between trials impossible. Outcomes may also be ‘cherry-picked’, such that favourable results are reported, and less favourable results withheld. The development of a minimum outcome reporting standard, known as a core outcome set, goes some way to addressing these problems. Core outcome sets are ideally developed using a patient-centred approach so that the outcomes measured are relevant to patients and clinical practice. Core outcome sets drive up the quality and relevance of research by ensuring that the right outcomes are consistently measured and reported in trials in specific areas of health or healthcare.

**Methods/Design:**

This is a mixed methods study involving three phases to develop a core outcome set for oropharyngeal cancer clinical trials. Firstly, a systematic review will establish which outcomes are measured in published oropharyngeal cancer randomised controlled trials (RCTs). Secondly, qualitative interviews with patients and carers in the UK and the USA will aim to establish which outcomes are important to these stakeholders. Data from these first two stages will be used to develop a comprehensive list of outcomes to be considered for inclusion in the core outcome set. In the third stage, patients and clinicians will participate in an iterative consensus exercise known as a Delphi study to refine the contents of the core outcome set. This protocol lays out the methodology to be implemented in the CONSENSUS study.

**Discussion:**

A core outcome set defines a minimum outcome reporting standard for clinical trials in a particular area of health or healthcare. Its consistent implementation in oropharyngeal cancer clinical trials will improve the quality and relevance of research.

**Trials and registration:**

This study is registered at the National Institute for Health Research (NIHR) Clinical Research Network (CRN) portfolio, ID 13823 (17 January 2013).

## Background

Around 1,500 cases of oropharyngeal squamous cell carcinoma (OPSCC) are diagnosed in the UK every year [1]. Treatment relies on radiotherapy (RT), surgery with or without post-operative RT or cisplatin-based chemoradiotherapy (CRT), CRT alone or following induction chemotherapy. Increasingly, small molecule adjuvants are also being used. Multi-modality therapy is associated, to varying degrees, with long-term deficits in speech and swallowing function, cosmesis and health-related quality of life.

While the incidence of squamous cancers at most sub-sites of the head and neck is decreasing, the incidence of OPSCC has doubled in the last decade; and this trend is seen throughout the developed world [2,3]. Oncogenic human papillomavirus type 16 (HPV-16) has been established as the causative agent and has given rise to a clinicopathologically distinct form of OPSCC that occurs in a younger patient population and is associated with improved survival outcomes, compared with HPV-negative disease [4,5].

Contemporary treatments for HPV-positive and HPV-negative OPSCC are, however, still the same and treatment survivors suffer from long-term sequelae of multi-modality therapy, to varying degrees. Clinical trials in HPV-positive disease are largely focused on deintensifying treatment to improve functional outcomes whilst maintaining the advantageous survival outcomes; however, current research in HPV-negative disease remains focused on improving survival outcomes, with less apparent focus on reducing toxicity and improving functional outcomes. This is largely due to the fact that overall survival rates for HPV-negative disease have remained stubbornly resistant to improvement for many decades.

Despite the fact that available treatments have a significant impact on functioning and quality of life, such outcomes are inconsistently measured and reported between trials. Additionally, there is no standardisation of outcome selection and reporting, even among trials of comparable interventions. This reduces the amount of data contributable for meta-analyses, leading to difficulties in interpreting treatment effect and in making evidence-based healthcare decisions. The development of a minimum outcome reporting standard for OPSCC clinical trials, known as a core outcome set, is one method proposed to address these problems.

A core outcome set defines the outcomes that should be consistently measured and reported in clinical trials in a specific area of health or healthcare. They are developed using consensus methods involving major stakeholders, such as patients and healthcare professionals, to ensure that the outcomes included are clinically relevant and therefore ‘core’.

The existence of a core outcome set does not mean that only these outcomes should be measured; however, if a minimum outcome reporting standard is adhered to, then there will be greater consistency of reporting in clinical trials and a greater body of evidence to contribute to meta-analyses to inform healthcare decisions. Additionally, the risk of outcome reporting bias is lessened by ensuring that outcomes are consistently measured and reported.

The earliest efforts to improve outcome measurement in clinical trials were made by the Outcome Measures in Rheumatology (OMERACT) collaboration in the early 1990s [6]. This international network developed core sets of measures for most of the major rheumatological conditions, and an observational review by Kirkham *et al*. demonstrated an increase in the consistency of outcome reporting across clinical trials in rheumatoid arthritis (RA) in the years following publication of the RA core outcome set [7].

The OMERACT collaboration has actively involved patients in discussions about which outcomes to measure in trials since 2002 [8]. Patient involvement was first proposed at the OMERACT meeting in 2000 when participants considered what might be a ‘clinically important change’ in response to treatment. It was realised that the perspectives of patients are important in developing core outcome sets, and they have been actively involved in, and significantly contributed to, all subsequent OMERACT meetings. Patients have enriched the OMERACT research agenda, provided insights into patient participation in research and stimulated patient involvement in health outcomes research more broadly [9].

Other bodies are now recognising the importance of involving patients in trial research. INVOLVE, the national advisory group for the promotion and advancement of public involvement in NHS, public health and social care research, promotes the involvement of patients and the public in discussions about clinical trials because ‘they are the participants in trials and ultimately the people for whom research is aimed to benefit’ [10]. The Core Outcome Measures in Effectiveness Trials (COMET) Initiative advocates the involvement of patients and the public in decisions about which outcomes should be included in core outcome sets in specific areas of health or healthcare.

The measurement of patient-reported outcomes (PROs) in clinical trials has increased substantially in the last 20 years [11]. These subjective measures help evaluate the burden of disease and treatment from the patient’s perspective. The CONSORT group have recently published a PRO extension to their guidance that aims to improve the reporting of PROs in trials to facilitate the use of results in informing clinical practice and health policy [12].

Core outcome sets are now in development in a number of clinical areas and their use is advocated, in the UK, by the National Institute for Health Research (NIHR) Health Technology Assessment (HTA) and the Cochrane Collaboration [13,14]. Core outcome sets will only influence the evidence base if they are actually implemented, and as core outcome set developers we must therefore actively engage with trialists, Cochrane Review Groups, clinical guideline developers, research funders, journal editors, regulators and trial registries to act as advocates to ensure that their use is encouraged and supported.

### Study overview

The objective of the CONSENSUS (Squamous Cell CarcinOma of the OropharyNx: Late PhaSE CliNical TrialS; Core OUtcomeS) Study is to develop a core outcome set for OPSCC clinical trials. This protocol presents the methodology to be used.

The first stage of the study will establish the current standard of outcome reporting in clinical trials through a systematic review of OPSCC randomised controlled trials (RCTs). The second stage will involve qualitative interviews with OPSCC patients and carers to establish which outcomes are important to these key stakeholders. The third part of the study will employ an iterative consensus technique known as a Delphi study. We expect that different stakeholder opinions about which outcomes should be measured in clinical trials in OPSCC will converge to achieve consensus on the outcomes in the OPSCC core outcome set.

## Methods/Design

CONSENSUS is a mixed methods study. The Delphi questionnaire will be developed using a comprehensive list of outcomes identified from a systematic review, and outcomes identified from qualitative interviews with OPSCC patients and their carers.

Ethical approval for this study was granted in the UK by the Liverpool Central Research Ethics Committee (reference 12/NW/0708). Approval at the University of Texas MD Anderson Cancer Center (Houston, TX, USA) was provided by the Institutional Review Board (protocol number 2013-0285).

### Systematic review

A systematic review will identify which outcomes are reported in phase III RCTs of interventions for the treatment of OPSCC. This review will be limited to English language studies published in the last 10 years.

### Search strategy

A broad-based search strategy will be used to identify all published OPSCC and squamous cell carcinoma of the head and neck (SCCHN) RCTs. This will be applied to PubMed, Embase and the Cochrane Central Register of Controlled Trials (CENTRAL) from 1 January 2003 to 14 May 2013 (Appendix A).

### Types of studies and interventions

Any phase III RCT of a treatment for OPSCC with curative intent will be included. Only SCCHN trials that comprise patients with OPSCC will be included.

### Types of participants

Adults aged over 18 years with OPSCC.

### Exclusion criteria

Studies without OPSCC patients, studies involving patients with recurrent or metastatic disease, and studies of interventions for the treatment of the side-effects of treatment, such as xerostomia.

### Eligibility of studies

Two reviewers (AW and a second reviewer) will independently assess the identified records. A large number of records will be identified by our search strategy, therefore studies will be excluded in three phases. All identified study titles will be reviewed and ineligible studies excluded. Studies that are eligible from the title or for which there is uncertainty will have their abstracts reviewed in the second phase. Again, studies that are eligible or for which there is uncertainty will have their full papers reviewed in the third phase.

In order to ensure accuracy of exclusion, a proportion of all included/excluded titles, abstracts and full papers will be reviewed by two senior authors ([name] and [name]).

A proportion of the studies excluded by title will have their abstracts reviewed. If more than 1% of these studies are found to be eligible then a further proportion of the same amount will be reviewed, until 1% or less of further studies in the re-review sample are eligible.

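### A pass on the 1% title-exclusion check does not show that the review is near complete, because the 1% is a share of excluded records and only the latest sample is judged

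*Protocol article*

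**What the plan says.** The Search strategy section sets out "to identify all published OPSCC and squamous cell carcinoma of the head and neck (SCCHN) RCTs". Eligibility is much narrower than the search: under Types of studies and interventions, "Any phase III RCT of a treatment for OPSCC with curative intent will be included", and the Exclusion criteria remove recurrent or metastatic disease and trials of treatments for side-effects.

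Under Eligibility of studies, the authors expect that "A large number of records will be identified by our search strategy" and therefore screen in three phases: title, abstract, full paper. Two reviewers work independently, and a title that leaves doubt goes forward to abstract review. Two senior authors look over a proportion of decisions at every phase.

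A separate paragraph then sets the check at issue. For some share of the records dropped on title alone, the abstracts are read as well. The rule is then: "If more than 1% of these studies are found to be eligible then a further proportion of the same amount will be reviewed", and this goes on "until 1% or less of further studies in the re-review sample are eligible". The article states no pooling of samples, no cap on their number and no confidence bound. It does not say that a failed sample leads to anything other than another sample.

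**The concern.** The rule has two features that weaken what a pass means.

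- **Denominator.** Completeness depends on missed trials as a share of all eligible trials. The rule measures missed trials as a share of excluded records. When the excluded pile is far larger than the set of eligible trials, 1% of the pile can be a large fraction of that set. The search is broad (the Embase trial filter, for instance, admits a record on the word three in its text) and eligibility is narrow, so the two denominators probably differ widely.
- **Stopping rule.** Each further sample is judged on its own and sampling ends at the first that passes. A process above tolerance therefore gets repeated chances to pass.

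What is at stake is mainly the review's account of how outcomes are reported and defined across trials (Study overview; Data analysis), for which it is the only source. A reader told that the check was passed could take the review to be nearly complete.

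**Working it through.** The article states no recall figure or sample size for this check, so there is no figure of its own to reproduce.

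**Inputs.** From the article: the 1% threshold, further samples of the same size as the first, and a stop at the first passing sample. Assumed, because not given: 1,000 to 10,000 records excluded by title (N), 30 to 200 eligible trials kept (K), samples of 100 to 1,000 (n).

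**1. Share of eligible trials missed at a residual rate of exactly 1%, a passing value.** Share = 0.01N / (0.01N + K).

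| N | missed (0.01N) | K = 30 | K = 50 | K = 100 | K = 200 |
|---|---|---|---|---|---|
| 1,000 | 10 | 25% | 17% | 9% | 5% |
| 2,000 | 20 | 40% | 29% | 17% | 9% |
| 5,000 | 50 | 63% | 50% | 33% | 20% |
| 10,000 | 100 | 77% | 67% | 50% | 33% |

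This needs no sampling error. It counts every abstract-eligible record as a missed trial. If, say, only half survived full-paper review, the cell N = 5,000, K = 100 would fall from 50/150 = 33% to 25/125 = 20%.

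**2. Chance of passing at a true rate of 2%, twice the tolerance.** A sample of n passes with at most 0.01n eligible records. With P the binomial probability of that, the chance within three samples is 1 − (1 − P)³. For n = 100: P = 0.98^100 + 100 × 0.02 × 0.98^99 = 0.133 + 0.271 = 0.403, and 1 − 0.597³ = 0.79. The last column is the exact one-sided 95% upper bound on the rate after a sample that just passes.

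| n | limit | first sample | within three | upper bound |
|---|---|---|---|---|
| 100 | 1 | 40% | 79% | 4.7% |
| 200 | 2 | 24% | 55% | 3.1% |
| 500 | 5 | 7% | 18% | 2.1% |
| 1,000 | 10 | 1% | 3% | 1.7% |

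**3. Finite pile, with found trials recovered.** This was simulated without replacement, 4,000 runs per setting, with 100 trials kept at first screening.

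- N = 2,000, n = 100, true rate 2% (40 missed at the start): the rule passed in every run and left on average 35 missed, 35/140 = 25% of eligible trials.
- N = 5,000, n = 250, true rate 1.5% (75 missed): it passed in every run and left about 62, 62/175, roughly 36%.
- N = 10,000, n = 1,000, true rate 2% (200 missed): it passed in only 7% of runs before the pile was fully re-read, and left on average about 7 missed, 2% of eligible trials.

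So the stopping rule does harm with small samples and works tolerably with large ones. The denominator problem remains at any sample size: with N = 10,000, n = 1,000 and a true rate of 1%, every run passed and 84 of 200 eligible trials (42%) stayed missed on average.

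**The case against.** The strongest reply is that this check is a backstop. Independent dual screening, forwarding of doubtful titles and senior review all come before it, and the stated aim of accurate exclusion is attached to the senior review rather than to the 1% rule. A true miss rate of 1% or 2% may therefore be unlikely. That stands as a point about likelihood. None of these safeguards carries a recall criterion, though, and none changes what the 1% rule accepts.

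The counts are assumed, and the unstated sample size is a detail that an article may leave to the full protocol. This also stands: the absent proportion is not the fault here, and with samples near 1,000 the repeated-sampling problem almost disappears. Small samples and very large piles should not be combined carelessly, since a sample of 100 from 10,000 would be only 1% of the pile.

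Three stronger readings are tempting, and the article supports none of them:

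- A reader might infer that a large share of trials is in fact missed. The article gives no counts from which to say so.
- A reader might infer that eligible trials found in a failed sample are thrown away. The text does not say this; they are presumably kept.
- A reader might infer that the Delphi long list is seriously depleted. Interviews and round 1 additions also feed it, and an outcome is lost only if no included trial or other source supplies it.

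**Conclusion.** The concern holds as a flaw in a rule that the article states. Passing the check is compatible with a material share of eligible trials being missed: about 5% to 77% at a residual rate of exactly 1% under the assumed counts, and lower after full-paper attrition. Judging only the latest sample adds a chance of false reassurance that is large for samples of 100 to 200, modest at 500 and negligible at 1,000. Both results are conditional on counts that the article does not give. They show what the rule tolerates, not what happened. The main consequence is for statements about the completeness of the review and about heterogeneity in reporting and definitions. The effect on the list of candidate outcomes is smaller.

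**What to change.** 1. Base the stopping decision on all re-review samples pooled. For example, samples of 100 with 3, 2 and 1 eligible records pass on the last alone, but the pooled rate is 6/300 = 2%.
2. State that every eligible trial found in any sample is kept.
3. In place of a bare 1% pass, report the estimated number of eligible trials missed (pooled rate × records excluded, noting how many of these the samples recovered), its one-sided 95% upper bound, and the implied sensitivity against trials included.

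Pooling limits the gain from repeated tries but cannot rescue a small first sample. With n = 100 and a true rate of 2%, the pooled limits are 1/100, 2/200 and 3/300. A pass at the second look needs 2 then 0 eligible: 0.273 × 0.133 = 0.036. A pass at the third needs a total of 3 after two failed looks, then 0: (0.273 × 0.271 + 0.182 × 0.133) × 0.133 = 0.013. The chance within three looks is 0.403 + 0.036 + 0.013 = 45%, against 79% under the present rule. This is why the upper bound has to be reported as well.

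The cost is possibly some further abstracts to read and a less favourable completeness statement. The search closed on 14 May 2013 and Delphi recruitment is being prepared (Trial status), so screening may be finished. In that case the samples already read can be pooled and re-reported at almost no cost.

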### Data extraction

Outcomes will be identified within the methods and results section of each paper, and for each outcome we will assess how it was defined and measured, the number of participants in which it was measured, whether it was measured using a validated tool, and whether it was stated in both the methods and results. The individual outcomes will be categorised under broader outcome domains.

### Data analysis

All eligible studies will be tabulated, and the identified outcomes presented along with their definitions and method of measurement. We also wish to identify any heterogeneity in the definitions of outcomes and the way in which they are measured. Scoping searches have suggested that outcomes with the same name are often defined or measured in different ways. We therefore wish to establish whether outcomes are defined and, if they are, whether there is heterogeneity in these definitions between studies which would make comparison of these outcomes between trials more difficult, if not impossible.

The identified outcomes will be categorised under broader outcome domains which will be decided upon by the study team. For functional outcomes, this process will be guided by the International Classification of Functioning, Disability and Health (ICF) categories for head and neck cancer [15].

### Qualitative interviews

The objectives of the qualitative part of the study are to establish which outcomes are valued by patients and carers, and which outcomes they feel should be included in a core outcome set. The journey from diagnosis through treatment is often a turbulent one for patients with OPSCC and qualitative methods will be particularly useful in helping us to understand their experiences of treatment. Spouses will also be interviewed as they almost universally become carers to their partners during this time and can provide an expert witness account of events whilst helping to contextualise the importance of different outcomes.

### Participants

Patients with OPSCC and their carers will be recruited to participate in qualitative interviews, from two centres in the UK and one in the USA. A carer is defined as a family member or spouse who provides informal care to the patient during their treatment and recovery. Patient and carer participants will be recruited from SCCHN survivorship clinics. Patient participants will be adults, aged 18 to 100 years, who are English speaking and up to 5 years post-treatment for OPSCC. Carers of eligible patient participants will also be invited to interview.

Eligible patients will be recruited from the outpatient clinic in a chronological order to avoid the risk that clinic staff will ‘cherry-pick’ patients who they anticipate will present a favourable account of their experiences. We will monitor the clinical and socio-demographic characteristics of our patient sample, and ensure maximum diversity in terms of the following characteristics: age, gender, sub-site, stage, HPV status, treatment modality and length of time since treatment. Maximum diversity sampling, a type of purposive sampling, is widely used in qualitative research with the aim of accessing a range of perspectives on the topic under investigation [16]. We will interview NHS patients in the UK, for whom care is provided free at the point of delivery and patients attending the University of Texas MD Anderson Cancer Center, which is a fee-paying institution. The UK and US groups will differ in their socio-economic circumstances, thus the sample encompasses diversity on this characteristic, which is well-recognised as having a significant impact on outcomes in SCCHN patients [17].

HPV status will not be available for patients whose diagnosis and treatment preceded testing for HPV. However, we will endeavour to recruit a mix of HPV-positive and HPV-negative patients.

We expect to recruit around 30 patients and carers in total, although this may change depending on early analyses.

